### Study Design

This study is a parallel-group, randomized controlled superiority trial with two groups (ie, intervention and control) having an allocation ratio of 1:1. The trial was registered at ClinicalTrials.gov (NCT04216446) on January 2, 2020. The intervention to be tested is an mHealth program that was developed locally to collect dietary, supplement use, and physical activity information from pregnant women and to provide personalized counseling tailored to the screening information. The control group will receive standard counseling with similar content, but the content will not be personalized and will be delivered through face-to-face sessions.

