### Enrollment Criteria

Pregnant women 18 years or older and in their first trimester are eligible to participate if they possess a personal smartphone with internet connection and agree to remain in the study until 1 year following the birth of their baby. Pregnant women on dietary control secondary to the diagnosis of diabetes mellitus; taking medications, such as antiplatelet aggregators, hypoglycemic drugs, or antihypertensive drugs; who have autoimmune, liver, or kidney disease; or who are unable to read and write due to a language barrier will be excluded from the study.

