### Sampling Strategy and Randomization

Participants were identified using a purposive sampling strategy and were randomly assigned to the study groups using simple block randomization (block size of 6). The Clinical Trials Unit at AKUH facilitated the computer-generated randomization and provided opaque, sealed envelopes to the research team to ensure concealment of the assignment (Figure 1).

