### Follow-Up

Follow-ups will be done four times, every 6 weeks: 6, 12, 18, and 24 weeks from the time of enrollment in the first trimester to monitor improvement, if any. For the intervention group, results of each follow-up and their comparison with the earlier one will be displayed on each participant’s personal page of the app. A summary of the individual results will be able to be viewed at any moment by the participant and handed over or shared with their obstetrician by email for further assessment and care. The control group will receive face-to-face counseling at each follow-up.

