### Expected Secondary Outcomes

#### Maternal Health

The following four maternal conditions will be identified through the medical records.

Pre-eclampsia will be defined as new onset of hypertension after 20 weeks of gestation along with proteinuria (ie, a spot urine protein to creatinine ratio of ≥30 mg/mmol) and/or evidence of maternal acute kidney injury, liver dysfunction, neurological features, hemolysis or thrombocytopenia, and/or fetal growth restriction [62].

Gestational hypertension will be defined as new onset of hypertension (ie, blood pressure of ≥140 mm Hg systolic or ≥90 mm Hg diastolic at or after 20 weeks’ gestation) [62].

Gestational diabetes will be defined as diagnosis made by a single-step 75-g oral glucose tolerance test conducted between 24 and 28 weeks of gestation or at any other time, with one or more of the following results: (1) fasting plasma glucose of 5.1 to 6.9 mmol/L (92-125 mg/dL), (2) 1-hour post–75-g oral glucose load of ≥10 mmol/L (180 mg/dL), and (3) 2-hour post–75-g oral glucose load of 8.5 to 11.0 mmol/L (153-199 mg/dL) [63].

Due to the expected low incidence of these conditions and given our small sample size, we shall pool these conditions as adverse maternal outcomes.

Gestational weight gain will be determined from weights recorded during the first, second, and third trimesters. Centiles and *z* scores will be assessed using the international gestational weight gain calculator based on the INTERGROWTH-21st (International Fetal and Newborn Growth Consortium for the 21st Century) Project standards for gestational weight gain [64,65].

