### Statistical Analysis

Data will be entered and analyzed using Stata software (version 12; StataCorp LP). Data from the intervention group will be digitalized and uploaded to the app. Categorical variables will be reported as frequencies and percentages. Continuous variables will be reported as means and SDs or medians and IQRs, as appropriate. General characteristics, nutritional change in the form of dietary risk score, supplement use, maternal outcomes, gestational weight gain, birth weight and length, BMI, and blood pressure will be compared using chi-square tests for proportions and *t* tests and Mann-Whitney *U* tests for continuous variables. A mixed-model method will be used to take into account the repeated measurements and correlation while modeling the fraction that scores adequately at each of the follow-up time points. In order to minimize selection bias, we will use multiple imputation models to handle missing data from participants who prematurely leave the study. Possible confounding variables, such as age, BMI, parity, previous history of miscarriage, socioeconomic status, educational status of the women, and occupation, will be assessed and adjusted. Moreover, interactions will be reported if present in the model.

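### Gestational age at enrolment is not named among the adjustment variables, although visits are timed from an enrolment that can fall anywhere in the first trimester: a small loss of precision, not a bias

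*Protocol article*

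**What the plan says.** - **Entry.** Under Enrollment Criteria, "Pregnant women 18 years or older and in their first trimester are eligible". No lower or upper gestational week is given.
- **Visit clock.** Under Follow-Up, visits take place "6, 12, 18, and 24 weeks from the time of enrollment in the first trimester", not at fixed gestational weeks.
- **Allocation.** Study Design describes a "parallel-group, randomized controlled superiority trial with two groups (ie, intervention and control) having an allocation ratio of 1:1". Randomisation is in blocks of six, and no stratification by gestational week is mentioned.
- **Adjustment.** Statistical Analysis says it will assess and adjust for "Possible confounding variables, such as age, BMI, parity, previous history of miscarriage, socioeconomic status, educational status of the women, and occupation". These seven variables are offered as examples. Gestational age at enrolment is not one of them.
- **Outcomes.** The abstract defines the diet and supplement outcomes as changes in score. The mixed model in Statistical Analysis instead takes the proportion of women with an adequate score at each visit, which is a level.
- **Weight gain.** Maternal Health says "Gestational weight gain will be determined from weights recorded during the first, second, and third trimesters", and then plans centiles and z scores on the INTERGROWTH-21st gestational weight gain standards. The secondary objective speaks of a mean gain, and Statistical Analysis lists weight gain among the two-sample comparisons.

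**The concern.** Enrolment week fixes where in pregnancy each of a woman's measurements falls. If diet, tablet use or activity depends on the stage of pregnancy, entry week explains part of the variation between women at a given visit. A model without it leaves that part in the error term. It also leaves any chance difference between the arms in entry week uncorrected. The protocol names its adjustment variables but not the one that its own visit schedule makes relevant to every repeated measurement. At stake is some precision in the primary comparisons.

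**Working it through.** **The plan's own figures.** The article gives no figure on this point. Its sample sizes do reproduce: the two-proportion formula with continuity correction, two-sided 5% and 80% power, gives 45 per group for 20% against 50% and 107 per group for 36% against 56%. Neither figure depends on covariates, so nothing stated changes.

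**Spread between women (assumed, because the article gives no entry distribution).**
- The maximum gap is the width of the entry window: 5 weeks if entry runs from 8 to 13 weeks, 8 if from 5 to 13, and 10 if from 4 to 14.
- With entry from 5 to 13 weeks, the four visits fall at 11–19, 17–25, 23–31 and 29–37 weeks of gestation.
- For uniform entry over width w, SD = w/√12. This gives 5/√12 = 1.44, 8/√12 = 2.31 and 10/√12 = 2.89 weeks. With w = 8, the average gap between two women is 8/3 = 2.7 weeks.

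**Spread between arms.** SE of the difference in mean entry week = SD × √(1/n₁ + 1/n₂).
- 150 against 150 (300 split 1:1), SD 2.31: 2.31 × √(2/150) = 0.27 week, 95% range ±0.52.
- 108 against 126 (after the reported losses of 42 and 24), SD 2.31: 0.30 week, ±0.59, if loss is unrelated to entry week.
- Over all the windows tried, the 95% limit runs from ±0.33 to ±0.74 week.

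**Gain from adjustment in a linear model.** If entry week has correlation r with the outcome, given the other terms in the model, the SE is multiplied by √(1 − r²), which is worth r² of the sample.

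| r (assumed) | SE ratio | Share of sample | Women, of 300 |
|---|---|---|---|
| 0.1 | 0.995 | 1% | 3 |
| 0.2 | 0.980 | 4% | 12 |
| 0.3 | 0.954 | 9% | 27 |

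**Bias and type I error.** Simulation with 150 per arm, entry uniform over 5–13 weeks and 5,000 runs per setting.
- No true effect: the mean unadjusted estimate was 0.0004 SD (r = 0.2) and 0.0009 SD (r = 0.4). The unadjusted test rejected in 0.055 and 0.050 of runs, against 0.051 and 0.049 with adjustment. The Monte Carlo error is √(0.05 × 0.95/5000) = 0.003.
- True effect 0.35 SD: the mean unadjusted estimate was 0.353 and 0.349. Power rose with adjustment from 0.863 to 0.875 at r = 0.2, and from 0.861 to 0.911 at r = 0.4, which lies above the range used in the conclusion.

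**Changes against levels.** If an outcome follows a + b × gestational week, the change over 24 weeks is 24b whatever the entry week, and adjustment gains nothing. The level at that visit is a + b × (entry week + 24), which does depend on entry week. The gain therefore applies to the mixed model of levels, and to change scores only if the trajectory is curved.

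**Raw weight gain.** R² = (slope × 2.31)²/SD². An assumed 0.3 kg per week of later entry with SD 6 kg gives 0.013; 0.5 kg per week with SD 4 kg gives 0.083. This concerns raw kilograms only, not z scores.

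**The case against.** The strongest reply has four parts.

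1. **The list is open and the article is condensed.** The full covariate set may sit in an analysis plan that is not shown. This stands. A reader might infer that women some eight weeks apart will be compared with no adjustment at all. The article does not say so: it only fails to name this variable, and eight weeks is an assumed extreme between two individuals.
2. **The trial is randomised.** A reader might infer a biased treatment effect. The calculations do not support that. Entry week is balanced in expectation, the unadjusted estimate is unbiased, and the standard error already covers chance imbalance. This stands in full and limits the point to precision.
3. **The outcomes are changes over fixed intervals, so linear drift cancels.** This is right for change scores, but it does not cover the mixed model, which analyses a level at each visit. That outcome is binary, however, so the linear-model percentages are only a guide there. With a logit link, adjustment would also make the odds ratio conditional on entry week.
4. **Weight gain is already standardised by z scores.** This stands for the z scores. It does not cover a two-sample comparison of raw mean gain, which the secondary objective and the analysis section leave possible.

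A further inference would be that the unequal losses (42 against 24, with miscarriage among the reasons) unbalance entry week among the women who remain. That is plausible, but the article reports no entry week for those lost, so it cannot be asserted. It is a reason to put the variable in the imputation model.

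**Conclusion.** The point holds as a minor, free improvement. Entry spans the first trimester, visits run from enrolment, and a baseline variable known for every eligible woman is not named for adjustment. Validity and the stated sample size are unaffected. The gain is about 1% to 9% of the sample for an assumed correlation of 0.1 to 0.3 in a linear model, and close to nothing for a change score if the trajectory is straight. The article gives neither the entry distribution nor any correlation, so these ranges rest on assumption.

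**What to change.** - Name gestational age at enrolment, in completed weeks and as a linear term, as a prespecified baseline covariate in the models for dietary risk score, supplement score and activity minutes, and in the mixed model of the proportion with an adequate score.
- Include it in the multiple imputation model. Under the assumed 5–13 week window, the latest entrants reach the fourth visit at 37 weeks, so delivery before that visit, and hence missing data, may depend on entry week.
- For weight gain, compare the INTERGROWTH-21st z scores already planned. If raw gain is also compared, replace the two-sample test with a model adjusted for gestational age at enrolment.

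The cost is one degree of freedom per linear model and no new data, because the value is needed to confirm eligibility. It should be fixed before the arms are compared, since the trial is not blinded.

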### Limitations

There are few anticipated limitations of the study. Firstly, the randomization ensures that unknown variables and confounders are randomly distributed among the two groups; however, there could exist residual confounding if not enough data are collected for the confounder in question or if the categories formed are too broad or narrow. Secondly, there could be information bias given that the assessment of behaviors during pregnancy is subjective and, therefore, could lead to differential or nondifferential misclassification. For factors such as substance use and smoking, underreporting can be experienced since these are not socially desirable behaviors. Thirdly, participants may experience recall limitations during the assessment of diet, supplement use, and physical activity. However, in order to minimize the chances of recall bias, a food record diary will be provided to women to document accurate information. Fourthly, the study could experience attrition bias, due to multiple follow-ups and long duration. Fifthly, blinding was not possible owing to the behavioral nature of the intervention. Lastly, as the study will assess the efficacy of the intervention, generalizability will be limited.

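### Covariate adjustment is framed as assessing possible confounders from an open list, so the adjustment set in an unblinded randomised trial is left to the analysis; the main cost is forgone precision and avoidable analyst freedom

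*Protocol article*

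**What the plan says.** The Statistical Analysis section of the protocol article contains four relevant statements.

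- Covariates are introduced as "Possible confounding variables, such as age, BMI, parity, previous history of miscarriage", and the sentence ends by saying that "socioeconomic status, educational status of the women, and occupation, will be assessed and adjusted". Seven variables are named: age, BMI, parity, previous miscarriage, socioeconomic status, education and occupation. No criterion for inclusion is given.
- Between-arm chi-square, t and Mann-Whitney tests cover baseline and outcome variables in one sentence, which begins "General characteristics, nutritional change in the form of dietary risk score, supplement use, maternal outcomes".
- After the covariate sentence comes the statement that "interactions will be reported if present in the model".
- The mixed model is for the fraction of women scoring adequately at each follow-up.

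The Limitations section says that "the randomization ensures that unknown variables and confounders are randomly distributed among the two groups", then adds that "there could exist residual confounding if not enough data are collected for the confounder in question". It also says that "blinding was not possible owing to the behavioral nature of the intervention".

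**The concern.** Among all randomised women, a baseline difference between arms is a chance difference. Covariates in a randomised comparison are therefore best chosen in advance because they predict the outcome, and kept whatever the observed balance. Assessing variables for confounding and then adjusting is the logic of a cohort study.

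The wording leaves the set open in two ways: 'such as' allows variables that are not named, while 'possible' and 'assessed' allow named ones to be left out. Two things are at stake. If a covariate enters only when it looks imbalanced, most of the precision that adjustment offers is lost. And an undefined set gives the analyst a choice that a fixed set would remove, in a trial without blinding. This is more than a detail left to an analysis plan, because the article itself states the approach.

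**Working it through.** **The plan's own figures.** The article gives no figure for the covariate rule. Its sample sizes do reproduce: a two-sided 5% test of two proportions with continuity correction, 80% power and 1:1 allocation gives 45 per group for 20% vs 50% and 107 per group for 36% vs 56%, as stated. They assume no covariate adjustment.

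**Inputs.** From Results: 300 recruited, 66 lost (42 in the intervention group), 234 remaining. Assuming 150 per arm, 150 − 42 = 108 and 150 − 24 = 126 remain. From Statistical Analysis: seven named covariates, hence 2^7 = 128 possible subsets before any unnamed variable is considered. The share of outcome variance explained by the covariates (R²) is not in the documents and is assumed, with a range.

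**Chance imbalance.** With seven independent baseline tests at .05, the probability of at least one P < .05 under sound randomisation is 1 − .95^7 = 30.2%.

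**Precision.** Take a continuous outcome with SD 1 and an effect of .37 SD, set to give about 80% power unadjusted.

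- Unadjusted: SE = √(1/108 + 1/126) = .1311; .37/.1311 = 2.82; power ≈ Φ(2.82 − 1.96) = 80.6%.
- All seven, R² = .20: SE = .1311 × √.80 = .1173; .37/.1173 = 3.15; power ≈ Φ(3.15 − 1.96) = 88.4%.
- The same formula gives 84.5% at R² = .10 and 92.1% at R² = .30. It ignores the few degrees of freedom spent.

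A linear simulation (108 vs 126, R² = .20, 600 trials under the alternative) agrees:

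| Rule | Power |
|---|---|
| Unadjusted | 80.5% |
| All seven, always | 87.8% |
| Only those with baseline P < .05 | 80.5% |

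The Monte Carlo standard error is about 1.3 to 1.6 percentage points. Selection by imbalance thus recovers essentially none of the gain.

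**Type I error.** A second linear simulation used 8,000 null trials per setting, 234 women split equally and independent normal covariates (standard error about .25 points):

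| Rule | R² = .1 | R² = .3 | R² = .5 |
|---|---|---|---|
| Unadjusted | 5.4% | 5.2% | 5.3% |
| All seven, fixed | 5.5% | 5.4% | 5.4% |
| Baseline P < .05 | 5.2% | 4.6% | 4.0% |
| Change in estimate > 10% | 5.6% | 4.3% | 3.3% |
| Most favourable of 128 sets | 10.9% | 17.2% | 25.1% |

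Across the 128 sets the estimate spans a median of 0.09, 0.15 and 0.19 outcome SD at these R² values.

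Mechanical selection holds the error rate or becomes conservative. Only a search guided by the treatment result inflates it.

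**The case against.** The strongest case for the plan is that 'assessed' may simply mean measured. Seven variables are named, and no condition such as significance or imbalance is attached, although the next sentence is conditional where it deals with interactions. On that reading the named set is already prespecified. This has force, but 'possible' and 'such as' still leave the set open, so the sentence needs closing either way.

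Two stronger readings are tempting, and the documents do not support them.

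- A reader might infer that the baseline tests choose the covariates. The two sentences are separated by those on the mixed model and on imputation, and nothing links them.
- A reader might infer that the 5% error rate will be breached. That needs an outcome-guided search over covariate sets, which no section proposes. The absence of blinding is attributed to the nature of the intervention, Results reports follow-up counts rather than outcomes by arm, and Quality Assurance places the full analyses at the end of the trial. None of this shows that covariates would be picked with the treatment estimate in view.

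Two further objections stand in part. First, losses were unequal (42 of 66 in the intervention group), so imbalance among the women who remain need not be pure chance, and concern about confounding there is not misplaced. That is a reason to fix prognostic covariates in advance, not to choose them later. Second, the simulations are linear while the planned mixed model is for a fraction, so the power figures may not carry over.

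Finally, a condensed article may leave a closed list to an analysis plan. Silence would be no finding; here the article states an approach, and it is the approach that should change.

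**Conclusion.** The point holds in limited form. The plan describes confounder assessment from an open list where a fixed, prognostic set would be better. The expected cost is forgone precision, illustrated by about 88% against 80.5% power at an assumed R² of .20, together with analyst freedom that is easy to remove. Type I error inflation of about 11% to 25% is an upper bound for a deliberate search over 128 sets, not a property of the plan as written.

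The illustration rests on an assumed R², independent covariates, a continuous outcome, an effect of .37 SD and 150 women randomised per arm. The documents supply no R², so the size in this trial is unknown. The change is worth making because it costs almost nothing.

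**What to change.** Replace the covariate sentence with wording to this effect: every adjusted analysis uses the same fixed set, whatever the observed balance, namely age, BMI at enrolment, parity, previous miscarriage, socioeconomic status, education and occupation, plus the baseline value of the outcome where it is measured. Remove 'possible', 'such as' and 'assessed'. Label any other adjustment set a sensitivity analysis. Present baseline characteristics descriptively, without P values.

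The cost is one sentence and a few degrees of freedom; the seven variables are already named for adjustment, and Table 3 schedules diet, supplement use and physical activity at baseline. If a logistic link is used for the fraction scoring adequately, the adjusted odds ratio is conditional on the covariates rather than marginal, and the plan should say so.

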### Data Management, Confidentiality, and Privacy Protection

The intervention group will add data via their smartphones to the mHealth app, which will be protected by log-in ID and password. The data from the program will be uploaded to the web server in real time. The server will be managed by the DHRC team, with access available to the primary person responsible for management of the mHealth program. The data will be handed over to the principal investigator (PI) when requested or upon study completion.

The data from the control group will be gathered on a database built using Microsoft Access. The file will be password protected and access will be limited to the PI and research assistant. The consent forms and the completed food record diaries will be saved in a locker, which will be secured by a lock and key.

### Quality Assurance

To ensure the validity and accuracy of the trial implementation, hands-on training has been given to the research assistant for data collection and for use of the mobile app over the 5 training days using the manual of operations for data collection. Refresher trainings will be conducted every 3 months and as needed. The data collected will be checked every day for possible errors and rectification will be made on the spot. In order to promote participant retention, they will be encouraged to ask any questions. The project PI will closely monitor the study and oversee its smooth implementation. Moreover, regular project meetings will be held for progress monitoring and troubleshooting. Since we do not anticipate changes in the indicators at interim periods of the trial, we intend to conduct intention-to-treat and full analyses at the end of the trial. No adverse events related to the intervention are anticipated.

